**Sampling method**

Study participants will be recruited from all primary, secondary and tertiary care facilities within Blantyre district on a first come-first served basis. While this is a convenience sample based on self-selection, random assignment to treatment and control groups will counteract biases inherent to this approach. All participants are volunteers and agree to be assigned to either the treatment or the control group.

The required study population size for paired tests of correlated means was calculated using STATA 17 and is based on the following:

- Pre-post-treatment difference of 1.5 points on standard test scales
- Standard deviation of the difference = 6
- Power 80%
- Significance level 5%

This results in a minimum of 128 participants per study arm. Given the continuity experience – the proportion of participants completing the pre- and post-treatment assessments for depression, anxiety and stress – of 20-45% reported by Daley, Hungerbuehler et al. (2020), we assume that the dropout rate will be as high as 75% for at least one of the standard mental health assessments. This means that a sample of 512 participants will be required per study arm to yield an effective post intervention sample of 128. Furthermore, if 20% of potential study participants will not meet inclusion criteria or drop out for other reasons, about 640 people will need to be recruited initially per study arm. Therefore, the total number of participants for this study is 1280.

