**Main research objective**

The main objective of this study is to test the *null hypothesis that the use of a chatbot such as Vitalk over a period of eight weeks does not result in different mental health outcomes in a treatment and control group* of health workers in Malawi. The null hypothesis will be tested in a two-arm RCT comparing the pre-treatment to post treatment scores using standardized scales for depression, anxiety, resilience, and burnout.

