**Data analysis method**

Data analysis will begin after the final workshop is concluded . There will be no interim sharing or analysis of trial data other than monitoring sample size in the two treatment arms and data completeness and appropriateness per data analysis plan for the entire trial data set. Data monitoring will be done by the trial manager.

The data analysis will start with descriptive statistics and bivariable analyses for mental health outcomes, resilience-building behaviors, intermediate outcomes, and user and study characteristics (non-modifiable and modifiable factors). This will include tests for central tendency and distribution.

The difference between treatment and control arms in mental health outcome scores at baseline, mid-study check-in and end-of-study-will be calculated using a linear, mixed-effect model for longitudinal data (e.g., STATA *mixed* or SPSS *MIXED*) applying maximum likelihood estimation, which takes into account any time trends. This method will allow the simultaneous modelling across different time points and estimate the difference in outcomes between the treatment and control groups across the entire study period.

This study will utilize Interpretative Phenomenological Analysis (IPA) as the main method of analysis for the qualitative data that shall be collected during the focus group discussions. Content Analysis will also be utilized to evaluate the participants’ experience in relation to pertinent social and psychological theories in order to explain attitudes and stigma behaviors. This process will also help to identify solutions and interventions that can be applied in order to ensure increased willingness to properly support health workers facing mental health challenges and a reduction in stigma against mental illness.

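### The 128 per arm is sized for a one-group paired pre-post test, so the stated 80% power does not belong to the trial's between-arm hypothesis

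*Combined protocol and SAP*

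**What the plan says.** Sampling method names the calculation: "The required study population size for paired tests of correlated means was calculated using STATA 17". The effect is "Pre-post-treatment difference of 1.5 points on standard test scales" and the spread is "Standard deviation of the difference = 6", with 80% power and a 5% significance level. The section concludes: "This results in a minimum of 128 participants per study arm". It then allows for 75% dropout, so that "a sample of 512 participants will be required per study arm to yield an effective post intervention sample of 128", and for a further 20% loss, which gives 640 per arm and 1280 in total.

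Main research objective states the null differently: use of the chatbot "does not result in different mental health outcomes in a treatment and control group". Data analysis method follows that null. It plans a maximum-likelihood linear mixed model over baseline, mid-study and end of study, to "estimate the difference in outcomes between the treatment and control groups across the entire study period".

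The document gives no between-arm difference, no expected change among controls, no pre-post correlation and no two-sample calculation. It does not spell out how the mixed model handles the baseline score.

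**The concern.** A paired test asks whether one arm moved from its own baseline. The trial asks whether two arms moved by different amounts. With n per arm and SD of change s, the variance of one arm's mean change is s²/n. The variance of the difference between two independent arms is 2s²/n. A size that gives 80% power for the first question does not give it for the second when the effect and SD are the same. Attaching the words per study arm to the paired result does not turn it into a two-arm calculation.

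This is the only power statement in the plan, and every recruitment figure descends from it. A reader would take the trial to have an 80% chance of detecting a 1.5-point benefit over control, and nothing in the document supports that.

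**Working it through.** **Inputs from Sampling method.** Difference 1.5; SD of the difference 6; power 80%; significance 5%; 128 completers per arm; dropout 75%; further loss 20%. Sidedness is not stated.

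**1. Reproduce the plan's figure (one-group paired test).**
- Normal approximation, two-sided: n = [6 × (1.960 + 0.842) / 1.5]² = 125.6, so 126.
- Exact paired t-test, two-sided: power is 79.84% at n = 127 and 80.15% at n = 128. The smallest adequate n is 128, as stated.
- One-sided (normal approximation): about 99, which does not match. The plan's figure is therefore two-sided.
- Inflation: 128 / 0.25 = 512; 512 / 0.80 = 640; 2 × 640 = 1280. All exact.

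The arithmetic is right for the question it answers. The fault is the choice of contrast.

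**2. The same inputs in a two-arm comparison of change at week 9, unadjusted.** Here 1.5 is read as the between-arm difference in change and 6 as the SD of change in each arm.
- Standard error = 6 × √(2/128) = 0.75, against 6/√128 = 0.53 in the paired calculation.
- Power = Φ(1.5/0.75 − 1.96) = Φ(0.04) = 51.6%; exact two-sample t, 51.3%.
- Completers per arm for 80%: 2 × [6 × 2.802 / 1.5]² ≈ 252; exact t, 253.
- Difference detectable with 80% power at 128 per arm: 2.802 × 0.75 = 2.10; exact t, 2.11.

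**3. Week-9 score adjusted for baseline.** With the SD of change held at 6 and pre-post correlation r, the residual SD is 6 × √((1 + r)/2). The document gives no r, so the values below are assumed.

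| r | Residual SD | Power at 128 per arm | Completers per arm for 80% (normal) |
|---|---|---|---|
| 0.3 | 4.84 | 70% | 164 |
| 0.5 | 5.20 | 63% | 189 |
| 0.7 | 5.53 | 58% | 214 |

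**4. Averaging the mid-study and week-9 assessments.** This is closer to the planned model. It assumes compound symmetry and a constant 1.5-point effect at both follow-ups.
- Unadjusted: an SD of change of 6 means σ² = 36 / [2(1 − r)]. The variance of (mean of the two follow-ups − baseline) is σ² × 1.5(1 − r) = 27, so SD = 5.20 and power = 63% at any r.
- Baseline-adjusted: the residual variance is 9(1 + 2r). For r = 0.3, 0.5 and 0.7 the SD is 3.79, 4.24 and 4.65, and power is 88%, 80% and 73%.

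**5. Completion other than 25%.** Sampling method cites 20 to 45% from an earlier study of the app. For 512 per arm and the unadjusted week-9 test:
- 20%: 102 per arm, about 43% power.
- 45%: 230 per arm, about 76% power.
- 45% with the adjustment in step 3: 83% (r = 0.7) to 91% (r = 0.3).

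**6. Change among controls.** The 1.5 is a pre-post difference. If controls also improve, the between-arm difference is 1.5 minus their improvement. As an illustration, assume controls improve by 0.5. The difference is then 1.0, and unadjusted power is Φ(1.0/0.75 − 1.96) = Φ(−0.63), about 26%.

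**The case against.** The strongest reply is that 51% describes an analysis the plan does not propose. It needs three conditions: that 1.5 is the between-arm effect, that the test is an unadjusted comparison of week-9 change, and that only 128 per arm complete. The planned model uses three time points. With baseline adjustment and a constant effect it could reach 80% at a correlation of 0.5 and 88% at 0.3. The 75% dropout is also given as a worst case. This reply stands against any unconditional figure. It does not rescue the stated 80%, because the paired calculation used none of these features and the plan states neither a correlation nor its baseline handling. An effect that builds late would also yield less than step 4 shows.

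A reader might go further than the documents allow in four ways.
- **That the trial's real power is 51%.** That is one scenario among those above.
- **That 80% is out of reach because about 49% completion is needed (252/512) against a cited 20 to 45%.** The 49% applies to the unadjusted week-9 test only. With baseline adjustment, 164 to 214 completers suffice, which is 32 to 42% of 512 and inside the cited range.
- **That both arms are bound to drift.** The workshop and weekly emails might produce improvement in both arms, while excluding severe scorers could push regression to the mean towards worsening. The net direction is unknown.
- **That the trial will draw its conclusions from within-arm tests.** Data analysis method already specifies a between-arm model for the outcome scores. Nor does the plan say how a non-significant result would be read.

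**Conclusion.** The point holds as a mismatch between the sample size calculation and the trial's hypothesis, not as an error of arithmetic. The mismatch itself needs no assumption: 128 reproduces exactly as a one-group paired test, while the null and the analysis are both between-arm. The stated 80% therefore does not apply to the main hypothesis, and 512, 640 and 1280 inherit the problem.

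The size of the shortfall is conditional. On the plan's own 1.5 and 6, read as a between-arm difference and the SD of change, with 128 completers per arm and two-sided 5%:
- unadjusted week-9 comparison: about 51%;
- baseline-adjusted week 9: about 58 to 70% for assumed correlations of 0.7 to 0.3;
- both follow-ups averaged: about 63% unadjusted, or 73 to 88% adjusted over the same correlations, under compound symmetry and a constant effect.

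Completion above 25% raises these figures, and improvement among controls lowers them. The document does not supply enough to choose among them, so the plan has no valid power statement for its main question.

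**What to change.** Replace the paired calculation in Sampling method with a between-arm calculation matched to the planned mixed model. It should state:
- the assumed between-arm difference, as distinct from the change expected within an arm;
- the SD and the correlation between assessments;
- how baseline is handled, and whether the target contrast is week 9 or an average over both follow-ups;
- that the test is two-sided.

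Then restate the power for that difference, and the difference detectable with 80% power, at the planned 512 randomised and 128 completers per arm. Because the correlation is unknown, show a range such as 0.3 to 0.7. The unadjusted week-9 figures (about 51% for 1.5 points; about 2.1 points at 80%; 252 to 253 completers per arm for 1.5 points) can serve as a reference, labelled as such. They should not be presented as the power of the mixed model.

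The cost is one rewritten paragraph and, in most of the scenarios above, a less favourable stated figure. The restatement needs no additional participants and no change to the analysis model, beyond saying how baseline enters it.

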Resilience refers to the ability to withstand or adaptively recover from stressors. Resilience also promotes psychological and physical well-being. Resilience is negatively correlated with symptoms of generalized anxiety and posttraumatic stress and positively correlated with gratitude, optimism, and positive affect. The five characteristics of resilience are meaning and purposeful life, perseverance, equanimity, self-reliance, and existential aloneness (Wagnild, 2009a). Total scores are categorized as very low (14–56), low (57–64), on the low end (65–73), moderate (74–81), moderately high (82–90), and high (91–98). RS-14 has been validated and used in low and middle-income countries (Wagnild, 2009b; Siriwardhana, 2015)

*Oldenburg Burnout Inventory (OLBI)*

Burnout is linked to relatively high work requirements and limited resource availability for managing them, which leads to negative emotional states. Therefore, the discrepancy between resources and challenges creates a significant negative emotional state. The OLBI has 16 items, eight to describe exhaustion and eight to describe disengagement (Demerouti & Bakker, 2008). The questionnaire includes both straight and reversely worded items in both dimensions. Low, medium or high OLBI-D scores are based on scores above or below 1 standard deviation of the mean (mean= 2.15, SD = 0.52; ≤1.62= low, 1.63 to 2.67= medium, ≥2.68= high). OLBI has been validated and used in low and middle-income countries (Kaggwa et al., 2021).

Stress is not included in these assessments, because past evaluations have shown almost universally high stress levels pre- and post-intervention, which makes it impossible to use it as an outcome if there are no discriminating factors.

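### One null hypothesis rests on four scales with no primary scale, adjustment or rejection rule, and the shared planning figure does not fit the only OLBI metric the protocol shows

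*Combined protocol and SAP*

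**What the plan says.** The Main research objective section sets one null hypothesis, that eight weeks of chatbot use makes no difference to mental health outcomes. It is to be tested by "comparing the pre-treatment to post treatment scores using standardized scales for depression, anxiety, resilience, and burnout". The four areas are listed as equals here and again under Study period. None is called primary.

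The Sampling method section gives one set of planning inputs: "Pre-post-treatment difference of 1.5 points on standard test scales", "Standard deviation of the difference = 6", 80% power and "Significance level 5" per cent. It names no scale and does not say whether the 5% applies to each scale or to all of them together. The calculation is for a paired test, and "This results in a minimum of 128 participants per study arm".

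The Data analysis method section plans a linear mixed model comparing the arms on the outcome scores at baseline, mid-study and end of study. It gives no hierarchy among scales, no adjustment and no rule for turning four results into one decision.

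The Data collection instruments section puts GAD-7 (up to 21), PHQ-9 and RS-14 (14 to 98) on total scores. For OLBI it gives only the cut-offs for low, medium and high on the OLBI-D subscale, based on "mean= 2.15, SD = 0.52". That is an item-mean metric. Annex 1.2.3 says only that OLBI scores are collected.

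**The concern.** Two things are left open.

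- **The decision rule.** With four scales, one null and one 5% level, the natural reading of an unadjusted plan is that each scale is tested at 5% and a difference on any of them rejects the null. The error rate of that decision is then well above 5%. A difference on one scale out of four could be reported as the trial's main result.
- **The planning figure.** One difference and one SD stand for scales with different units. If OLBI is analysed as an item mean, an SD of change of 6 is out of reach, and the 80% power statement has no content for burnout.

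**Working it through.** **1. The plan's own figure.** Inputs from Sampling method: difference 1.5, SD of difference 6, power 80%, alpha 5% (taken as two-sided).

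- Standardised difference: 1.5 / 6 = 0.25.
- Paired t test: n = 128, power 80.2%. A one-sided test would give 101, so the two-sided reading is the one that fits.
- Inflation: 128 / (1 − 0.75) = 512; 512 / (1 − 0.20) = 640; 2 × 640 = 1280.

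The arithmetic is correct. The question is what it applies to.

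**2. Error rate if any one of four scales suffices.** For independent tests, the chance of at least one false rejection in either direction is 1 − 0.95⁴ = 18.5%. For a false result in Vitalk's favour, each two-sided test contributes 2.5%, so the chance is 1 − 0.975⁴ = 9.6%. The documents give no correlations between scales. The other rows come from simulation with equally correlated normal test statistics.

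| Correlation (assumed) | False rejection, either direction | False finding in Vitalk's favour |
|---|---|---|
| 0 | 18.5% | 9.6% |
| 0.5 | 15.6% | 7.8% |
| 0.7 | 13.0% | 6.5% |
| 0.9 | 9.4% | 4.7% |
| One test only | 5% | 2.5% |

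For correlations from 0.7 to 0, the ratio to the nominal rate is 13.0 / 5 = 2.6 to 18.5 / 5 = 3.7 in either direction. In Vitalk's favour it is 6.5 / 2.5 = 2.6 to 9.6 / 2.5 = 3.8.

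**3. The planning figure on the OLBI metric shown.** With the same SD, 0.52, at both times and correlation ρ between them, SD of change = 0.52 × √(2(1 − ρ)).

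- ρ = 0.5: 0.52.
- ρ = 0: 0.74.
- ρ = −1, the maximum: 2 × 0.52 = 1.04.

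The planned 6 is 6 / 1.04 = 5.8 times the maximum. A 1.5-point change is 1.5 / 0.52 = 2.9 SDs of the score. It is also wider than the whole medium band, 2.67 − 1.63 = 1.04.

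**4. The same figure on an OLBI sum score.** Suppose the item-mean SD of 0.52 carried over to the sum. Setting the SD of change to 6 gives ρ = 1 − 36 / (2 × SD²).

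- All 16 items: SD = 16 × 0.52 = 8.32, so ρ ≈ 0.74, which is feasible.
- One 8-item dimension: SD = 8 × 0.52 = 4.16, so ρ ≈ −0.04.

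The fit therefore depends on a score definition that the protocol does not give.

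**5. Price of adjustment.** Under Holm the smallest of four p-values must be below 0.05 / 4 = 0.0125. With 128 per arm and a standardised difference of 0.25:

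| Test | Power at 5% | Power at 0.0125 |
|---|---|---|
| Paired, as in the protocol, one scale | 80% | 62% |
| Between arms, one scale | 51% | 31% |

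If all four true between-arm effects are 0.25 SD of change, the power to reject on at least one scale under Holm is about 77% at correlation 0 and about 53% at 0.7 (simulated).

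**The case against.** Several counter-arguments have force.

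- **The protocol nowhere says 5% per scale.** True. It is inferred from a single level with no adjustment. A rule requiring all four scales to succeed would protect the 5%, but no such rule is stated, so the inference is fair and has to be labelled as one.
- **A reader might infer that the chance of falsely claiming Vitalk works is three to four times the stated 5%.** The documents do not support that. The 13% to 18.5% counts errors in both directions; a false finding of benefit runs at 6.5% to 9.6%. The right comparator for that is 2.5%.
- **A reader might add the mid-study assessment and quote 1 − 0.95⁸ = 34%.** That treats repeated scores on the same people as independent. It also assumes eight separate tests, whereas the Data analysis method section describes a model estimating the difference over the whole study period.
- **A reader might call the planning figure impossible for OLBI outright.** The SD of 0.52 is given only to band one subscale, and the outcome score is never defined. The misfit is certain only for the item-mean metric, with that SD at both times.
- **A reader might argue that 1.5 points is under 2% of the RS-14 range (1.5 / 84), so power for resilience is unsound.** Power depends on the SD of change, not the range, and the documents give no SD for RS-14. Nothing in the units argument disproves the figure for GAD-7, PHQ-9 or RS-14.
- **The fall from 51% to 31% mixes two issues.** The 51% arises because the sample was sized for a within-arm paired test while the analysis compares arms. That is a separate matter; the 80% to 62% comparison isolates the cost of adjustment.

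**Conclusion.** The point stands in two parts.

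First, the main null has no decision rule. If one scale at an unadjusted 5% is enough, the two-sided error rate is about 13% to 18.5% for assumed correlations of 0.7 to 0. It returns to 5% only if the four tests are perfectly correlated. That no scale is primary is confirmed only for the text available, which lacks the front matter.

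Second, the 1.5-point, SD 6 figure cannot support an 80% power statement for OLBI on the item-mean metric, taking SD 0.52 at both times. Whether it could on another OLBI score is open, because the outcome score is undefined.

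**What to change.** Before unblinding, add one of these rules to the Data analysis method section:

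- Apply Holm across the four week-9 between-arm contrasts, and reject the main null only if at least one Holm-adjusted p-value is below 5%.
- Or name one scale as primary, tested at 5%, and let the main null rest on it alone. Treat the other three as secondary, with Holm among them.

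In the Sampling method section, state which scale or scales the 1.5-point, SD 6 figure applies to. In the Data collection instruments section, define the OLBI score used as the outcome. Do not claim 80% power for OLBI on the item-mean metric from that figure.

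The change takes a few sentences and no new data. Holm costs power, as shown in step 5 of the working: the protocol's own paired test for a single scale drops from 80% to about 62% at the first step. Naming one primary scale avoids that loss, at the price of committing the main conclusion to one outcome.

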All participants will be asked to take the standard mental health tests again in week four or five of the trial. This will be done virtually though email to all trial participants as a mid-trial check-in. After the end of the 56-day period, in week nine, both the treatment and control groups will be invited to attend a concluding half-day workshop, during which they shall again be evaluated on their general mental health using the previously completed mental health assessment tools. They shall then complete an anonymous online questionnaire on their experiences of interacting with the app or accessing the referred mental health links. Some participants will be invited to take part in focus group discussions (FGD) aimed at gaining detailed feedback about their experiences of using the two different interventions and the Vitalk app specifically (treatment group participants only for the latter). A mix of in-person and anonymous virtual FGDs are planned given the sensitive nature of mental health. A virtual FGD would be done without video and participants would only be identified by number not name. The use of two FGD formats, in-person and virtual, allows the comparison of how responses may differ between these two approaches. This study concludes with the workshop and FGDs in the 9^th^-week.

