**Benefits/Impacts**

The primary benefit of involvement in this project is the anticipated mental health and wellbeing of participants. The overall aim of Vitalk is to improve wellbeing by reducing stress, anxiety and depression using a preventative approach to mental health, which the participants shall benefit from. Additionally, the participants will also benefit from the mental health presentations to be conducted at the workshops, in which the members of the Department of Psychology shall discuss various aspects of mental health and how it affects workplace performance and wellness.

Participants will receive an allotment of 10Gb data bundle allowance valued at K15,500 (about $20) with a selected mobile carrier to eliminate any barriers of accessing the internet during the trial. Those not using the preferred provider at the time of the trial will receive a free SIM card. If it is feasible for the mobile service provider to track whether Vitalk or the control group website were accessed, airtime allocations will be contingent on the use of Vitalk or the control group website. In addition, all participants will be reimbursed $10 for their transport and time, as well as the government rate lunch allowance of K4000 during the attendance of the introductory and concluding workshops.

In addition, and following common practice in clinical trials, participants will receive an appreciation allocation of about 5Gb airtime valued at K8,200 (about $10) at the end of the trial, the final workshop, in recognition of their time sacrifice and as appreciation of their contribution to science. This incentive will hopefully encourage participants in the treatment group to continue the use of the Vitalk app and participants in the control group to try out Vitalk.

1. **Research dissemination strategy**

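### Week-9 scores have no stated route for workshop non-attenders and the analysis has no missing-data sensitivity check, although loss of up to 75% is planned; bias could run either way

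*Combined protocol and SAP*

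**What the plan says.** - **Sampling method.** Planning assumes "we assume that the dropout rate will be as high as 75% for at least one of the standard mental health assessments". The figure rests on 20-45% completion of pre- and post-treatment assessments in an earlier uncontrolled study of the app. The stated response is to raise 128 per arm to 512, and then to 640 per arm (1280 in total) for ineligibility and other loss.
- **Study period, mid-study.** The week 4-5 tests go by email to all participants.
- **Study period, week 9.** The text says "both the treatment and control groups will be invited to attend a concluding half-day workshop, during which they shall again be evaluated". It gives no alternative for people who do not come.
- **Data management method and Annex 1.2.3.** Quantitative data are entered online, and contact details are held during the trial. The annex lists the four test scores among the data captured by the control website and by Vitalk.
- **Benefits/Impacts.** If the carrier can track access, "airtime allocations will be contingent on the use of Vitalk or the control group website". Separately, transport and lunch payments for the workshops and K8,200 of closing airtime are offered with no stated condition of use.
- **Study period, prompting.** The treatment arm is messaged daily for four weeks and then every other day, on top of weekly emails. The control arm gets the weekly emails only.
- **Data analysis method.** One linear mixed model covers baseline, mid-study and end of study, "applying maximum likelihood estimation, which takes into account any time trends". No missing-data assumption, comparison of people with and without final scores, or sensitivity analysis is given.

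**The concern.** Enlarging the sample restores the number of final scores. It does nothing about who supplies them. If three quarters of participants lack a week-9 score, the treatment effect rests largely on what the model assumes about them.

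Three features suggest that the loss may be related to engagement. The final tests sit inside an event that takes half a day. Scores are captured on the same platforms that deliver the interventions. Airtime may be withheld from non-users, which could reduce their completion of online tests. Because the arms are prompted at different rates, the link between engagement and being observed may also differ by arm. The mixed model as described does not include platform use, so it cannot allow for loss that depends on use beyond what the observed scores show.

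Two results are at stake. One is whether the reported difference describes offering Vitalk to all randomised health workers or only those who stayed engaged. The other is objective 1: airtime tied to use rewards the adoption and continuity which that objective measures.

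**Working it through.** **1. The plan's own figures.** Inputs from Sampling method: "Pre-post-treatment difference of 1.5 points on standard test scales"; "Standard deviation of the difference = 6"; 80% power; 5% significance, taken as two-sided. For a paired test the normal approximation is n = [6 × (1.960 + 0.842) / 1.5]² = 125.6, so 126. The exact t calculation gives 128 (power 0.80). Then 128 / 0.25 = 512, 512 / 0.80 = 640 and 2 × 640 = 1280. All four stated figures reproduce.

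**2. Retention range.** Completion of 20% to 45% would leave 512 × 0.20 = 102 to 512 × 0.45 = 230 final scores per arm. The planning value of 25% is near the low end.

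**3. Routes to a final score.** The mid-study tests have an emailed route for everyone, and data entry is online throughout. Week 9 has only the workshop. In-person attendance is not stated, but transport and lunch payments (Benefits/Impacts) and masks and distancing (Risks) imply it. A remote week-9 route therefore looks technically possible and is simply not provided.

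**4. How far the effect could move.** Let D be the between-arm benefit the model reports and p the proportion missing in each arm. Let dT and dC be the amounts by which missing treatment and control participants do worse than the model implies. The effect in all randomised is D − p × (dT − dC). Take D = 1.5 and p = 0.75. Both are assumptions: the plan states 1.5 as a within-arm change, and 75% is its upper figure for missing at least one assessment.

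| dT − dC | Effect in all randomised |
|---|---|
| −0.5 | 1.5 + 0.375 = 1.875 |
| 0 | 1.5 |
| 0.5 | 1.5 − 0.375 = 1.125 |
| 0.75 (missing gain half) | 0.25 × 1.5 + 0.75 × 0.75 = 0.94 |
| 1 | 1.5 − 0.75 = 0.75 |
| 1.5 (missing gain nothing) | 0.25 × 1.5 + 0.75 × 0 = 0.375 |
| 2 | 1.5 − 1.5 = 0 |

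Across the 20% to 45% completion range, the gain-nothing case runs from 0.20 × 1.5 = 0.30 to 0.45 × 1.5 = 0.675. The gain-half case runs from 0.30 + 0.80 × 0.75 = 0.90 to 0.675 + 0.55 × 0.75 = 1.09.

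**5. Direction.** A simulation applied maximum likelihood to the three visits. Assumptions, none of them in the documents except the SD and the 25% retention: true effect −1.5 (lower is better), SD of change 6, within-person correlation 0.5, 25% retained per arm, log-odds of being observed 1 per SD of engagement, and mid-study scores partly observed.

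| Relation of engagement to outcome | Estimate | Bias |
|---|---|---|
| Benefit tied to engagement in treatment only, 1.5 points per SD | −2.39 | overstated by about 0.9 |
| As above, mid-study scores complete | −2.29 | overstated by about 0.8 |
| Treatment only, 0.75 per SD | −1.93 | overstated by about 0.4 |
| 1.5 per SD in treatment, half that in control | −1.92 | overstated by about 0.4 |
| Same relation and same selection in both arms | −1.48 | none |
| Engagement unrelated to outcome | −1.55 | none material |
| Same relation, weaker selection in treatment (log-odds 0.5 against 1.5) | −0.82 | understated by about 0.7 |
| Less-well participants engage more in treatment | −0.62 | understated by about 0.9 |

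**The case against.** A reader might infer that missingness follows engagement and that the model therefore overstates the effect. The documents do not establish either step.

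- The model does not simply give absent participants the completers' result. It conditions on each person's observed scores, including the emailed mid-study test, and is valid if loss depends only on those scores. Similar selection in both arms cancels. This stands, and it rules out any claim about direction.
- The airtime condition applies only if tracking is feasible, and it covers both arms. Losing data would mainly hinder the emailed mid-study test and would not stop anyone being tested at the workshop. Workshop payments and closing airtime already reward attendance regardless of use. This stands. It does not help people who cannot attend, and the condition would matter more once a remote week-9 route exists.
- The footnote on extending the trial asks how access would look without airtime support. It does not show that a use condition has inflated engagement.
- The gain-nothing case is extreme and cannot be presented as the expected shortfall. This also stands.
- It is also tempting to argue from power: 128 completers per arm give 80% under the plan's paired calculation but only about 52% for a two-arm comparison of 1.5 points with SD 6. That drop comes from the choice of test and is a separate sizing question.

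The gap in the plan survives these points: there is no stated route for non-attenders and no check on the missing-data assumption.

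**Conclusion.** The point holds as a risk of unknown direction. The plan leaves avoidable and possibly informative loss of the final outcome, and relies on one model without testing the assumption that carries it. Overstatement is plausible if mainly engaged Vitalk users return; no bias and understatement are also possible. In the simulated scenarios the bias ran from about 0.9 points over to about 0.9 points under a true effect of 1.5. On the simple arithmetic, a 2-point shortfall confined to missing treatment participants removes a 1.5-point effect altogether. These sizes are illustrations. They rest on 75% loss in each arm, on reading 1.5 as a between-arm effect, and on assumed links between engagement, outcome and attendance. Uncertainty about direction is itself a reason to pre-specify a sensitivity analysis. The change is cheap and worth making.

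**What to change.** 1. **Week-9 route.** Send the tests by study-portal link, with reminders and a fixed window, to every randomised participant regardless of workshop attendance or platform use. Record the mode of completion. Report loss by arm and by engagement, counting separately those removed as high risk; the removal rule itself is not in question here.
2. **Incentives.** Drop the clause that ties airtime to use. Give the existing closing airtime for completing the week-9 tests by either route.
3. **Analysis.** State the missing-data assumption behind the mixed model. Pre-specify a sensitivity analysis for data missing not at random: delta adjustment with a tipping point, varied in both arms, and control-based imputation as one scenario. Use the engagement data listed in Annex 1.2.3 in the imputation model, and report the result beside the maximum likelihood estimate.

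**Cost.** The first item reuses the mid-study email procedure, the second is a change of wording and the third is one added analysis. There are three downsides. Week 9 will mix workshop and remote completion, and mode may be correlated with engagement, which is why it must be recorded. Some airtime will go to non-users. The sensitivity estimate may be less favourable and, with this much missing, will depend heavily on its assumptions, so a range should be shown.
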